### Procedure

Eligible individuals enrolled in the study will be randomized, using a computer-generated random number sequence, to receive MIGT along with either oxytocin or placebo administration prior to each session. Each member of a specific MIGT cohort will receive the same study drug as the other members of that cohort, and members of each MIGT cohort will receive the same study drug for all six sessions. Blinding procedures will be controlled by Wellspring Compounding Pharmacy (Berkeley, CA, USA).

Previous work has shown that intranasal oxytocin administration begins to have physiological effects within 30 min and lasts for at least 90 min [35]. Thirty minutes prior to beginning each MIGT session, the study physician will administer the study drug (Wellspring Compounding Pharmacy, Berkeley, CA, USA) intranasally using a mucosal atomization device (MAD300; Teleflex technologies, Mooresville, NC, USA) attached to a 1-mL Luer-lock syringe. The oxytocin will be prepared as 40 International Units (IU) of oxytocin per 1 mL. Participants will receive 1 mL total, with 0.5 mL administered in each nostril using two separate syringes (with 0.06 mL additional drug in the first syringe to account for the MAD300 dead space). The administration procedures are consistent with recommendations for standardized intranasal drug administration [64]. Study drug administration will occur with all members present in the group therapy space, and the order of administration to individuals within a cohort will be randomized at each session.

To test tolerability to the study drug, participants will complete an Oxytocin Side Effect Checklist (OTSE), a list of 21 possible side effects [37] and the opportunity to report any other adverse effects, after each MIGT session. In addition, participants will be asked after each session to guess whether they have received oxytocin or placebo.

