#### Self-assessment measures

Participants will complete self-assessment measures on Google Nexus 7 Tablets via Research Electronic Data Capture (REDCap), an online data capture tool, hosted by the University of California, San Francisco. At the initial visit, participants will be asked their preferred term for methamphetamine, and all future references to the drug in self-assessment questionnaires will use the individual respondent’s preferred term. The timing of administration of self-assessment measures is shown in Fig. 2.
*Social and group cohesion measures*
1.1The Group Questionnaire (GQ) [69], a 30-item measure of the quality of the therapeutic relationships in a group setting1.2The Social Provisions Scale (SPS) [70], a 24-item measure of the degree to which respondents’ social relationships provide various dimensions of support1.3The Inclusion of Others in the Self (IOS) [71], a measure assessing perceived interpersonal connectedness to various “others” for which respondents choose one in a series of images of increasingly overlapping circles. The current study measures participants’ relationships with: methamphetamine, methamphetamine-using communities, the LBGTQ community, their most intimate relationship, and their family of origin. The final administration of this questionnaire also asks about their relationship with their MIGT cohort for the study1.4The Sexual Risk-Taking Behavior (SRTB) questionnaire [9, 72] will be used to conduct a structured interview to assess risky sexual behaviors over the past 6 weeks. This measure asks the same questions regarding sex while sober and sex while under the influence of methamphetamine

*Stress reactivity measures*
2.1The Six-Item State-Trait Anxiety Inventory Short Form (STAI-6) [73], a validated measure of the three highest anxiety-present and three highest anxiety-absent items from the state portion of the full State-Trait Anxiety Inventory [74]

*Substance use measures*

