### Data Analysis Plan

Descriptive statistics will be used for demographic information and other baseline characteristics. Our dichotomous primary outcome measure (in attendance/absent) will be compared between oxytocin and placebo treatment conditions using generalized estimating equations to accommodate for correlations among the observations originating from the same participant and correct for interdependence resulting from MIGT cohort membership. Secondary outcomes collected at each MIGT session consist of group cohesion as measured by the GQ, self-reported anxiety as measured by the STAI-6, psychophysiological measures (including heart rate, HF-HRV, and temperature), methamphetamine craving as measured by the MCQ-Br, and urine drug screen. Given the exploratory nature of this novel study design, we will use descriptive statistics and estimate Cohen’s *d* effect sizes for secondary outcomes. Effect sizes will be calculated by subtracting the mean change in the oxytocin group from the mean change in the placebo group and dividing by the pooled baseline standard deviation. If there is substantial missing data, we also will consider using mixed linear models or multiple-imputation techniques to estimate mean change values in each treatment group with greater accuracy. Additional exploratory outcome measures collected at two timepoints, baseline and after the final MIGT session, consist of the SRTB, SPS, IOS, and RTCQ and will be processed using the same methodology. Results of secondary outcomes will be considered exploratory, and further confirmatory studies would be needed to confirm the results. ECR-S, ACE, STAI, and subsections of the ASI-Lite, along with baseline measurements of the SPS, IOS, SRTB, and RTCQ, will be explored as potential predictors of oxytocin response using Pearson’s correlation coefficients.

In addition to utilizing psychophysiology measures recorded during MIGT sessions as a secondary outcome variable in our main data analysis approach, we will utilize models designed to explore physiological synchrony, contagion, and other aspects of shared physiological states [84].

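### The change-from-baseline effect size cannot be applied to group cohesion (GQ) or the IOS cohort item, because neither can have a pre-drug baseline

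*Protocol article*

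**What the plan says.** The Data Analysis Plan introduces the per-session outcomes thus: "Secondary outcomes collected at each MIGT session consist of group cohesion as measured by the GQ", followed by anxiety, psychophysiology, craving and the urine screen. It then gives a single estimator for all of them: "Effect sizes will be calculated by subtracting the mean change in the oxytocin group from the mean change in the placebo group and dividing". The divisor is the SD at baseline, pooled over the arms.

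A baseline timepoint is named only for a separate set: "Additional exploratory outcome measures collected at two timepoints, baseline and after the final MIGT session, consist of the SRTB, SPS, IOS, and RTCQ". These are to be handled by the same method. Under Self-assessment measures, however, the IOS gains a question at the end: "The final administration of this questionnaire also asks about their relationship with their MIGT cohort for the study".

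On timing, the Procedure section states: "Thirty minutes prior to beginning each MIGT session, the study physician will administer the study drug". It adds that "members of each MIGT cohort will receive the same study drug for all six sessions", and that intranasal oxytocin "begins to have physiological effects within 30 min and lasts for at least 90 min". No undosed session is described.

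The last paragraph of the Background makes it an aim to estimate effect sizes, group cohesion included, for use in future trials.

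**The concern.** Both parts of the stated d depend on a baseline: the numerator is a difference in change, and the denominator is a baseline SD. For a measure that first exists after dosing, the only candidate baseline is itself a treated value. Subtracting it removes whatever difference between arms is already present at that point. The protocol's own account of a rapid onset makes such an early difference plausible.

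No hypothesis test is at stake. What is at stake is the accuracy of an effect size the trial sets out to deliver. A cohesion effect that appeared early and persisted would be reported as small or absent, and that figure could then be used to size the next study.

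**Working it through.** **1. The document's own figures.** It gives no number for the secondary effect sizes. Its only effect-size figures are in the Power analysis section: with 25 per arm and two-sided alpha 0.05, more than 99% power at d = 1.44 and 80% at d = 0.81. A two-sample t-test gives 99.9% and 80.1%, with a minimum detectable d of 0.809. These figures reproduce, concern attendance and are not affected here. The value 0.81 is used below only as an illustrative effect size.

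**2. Can a pre-drug GQ value exist?**
- The GQ asks about relationships in the therapy group (Self-assessment measures).
- Cohorts are closed and run for six sessions (Motivational interviewing group therapy).
- Drug is given 30 minutes before each session, with the members already in the group room (Procedure).

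The group's first meeting therefore takes place under study drug. The assessment timetable (Fig. 2) is not available in the text, but no timetable could supply a rating of a group that has not yet met.

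**3. What the formula returns if session 1 is the baseline.** Let the true between-arm difference be D at the final session and fD at session 1, both in SD units, with sign set aside:

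- Difference in mean change = D - fD = D(1-f).

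| Assumed D | f = 0 | f = 0.25 | f = 0.5 | f = 0.75 | f = 1 |
|---|---|---|---|---|---|
| 0.5 | 0.50 | 0.375 | 0.25 | 0.125 | 0 |
| 0.81 | 0.81 | 0.608 | 0.405 | 0.203 | 0 |
| 1.44 | 1.44 | 1.08 | 0.72 | 0.36 | 0 |

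**4. Simulation check.** Settings: 25 per arm, 10,000 runs, D = 0.81, correlation between the two sessions of 0.3, 0.5 or 0.7, equal SDs and no cohort effect.

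| f | Change-based d (range over correlations) | Final-session d (range over correlations) |
|---|---|---|
| 0 | 0.819 to 0.826 | 0.822 to 0.827 |
| 0.5 | 0.412 to 0.414 | 0.825 to 0.827 |
| 1 | 0.00 | 0.823 to 0.826 |

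Values slightly above 0.81 reflect the usual small-sample bias of Cohen's d: with 48 degrees of freedom, 0.81/(1 - 3/191) = 0.823. The comparison of final-session values recovers D whatever f is. The change-based d does so only when f = 0.

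**5. The IOS cohort item.** It has one administration, at the end. A change score needs two, so the formula has no value for this item.

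**The case against.** **Other in-session measures.** A reader might infer that every measure taken at the sessions lacks a pre-drug baseline. The document does not support that.
- A urine sample is taken at the initial visit.
- The full State-Trait Anxiety Inventory, whose state portion is the source of the six short-form items, is listed with the screening variables.
- Psychophysiology has a 5-minute baseline recording; its order relative to the spray is not stated, so it cannot be called post-dose.
- Timing of the craving scale is left to Fig. 2, which is not shown.

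**Loss of the effect as a certainty.** A reader might also infer that a real cohesion effect will be reported as zero. The text never names session 1 as baseline, and total loss requires f = 1, a full separation of the arms after one session. The description of the therapy presents cohesion as something built in the early group phases, which makes f = 1 an extreme case. A narrower range can be obtained by assuming a particular shape (a linear rise from D/6 to D would keep 5/6, or 83%), but nothing in the document favours that shape. At f = 0 nothing is lost.

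**Mitigation.** Descriptive statistics are planned as well. If shown by arm and session, they would reveal a constant GQ difference beside a small d. The IOS cohort question is an addition to a scale otherwise given twice, and the authors may intend only to describe it. All these outcomes are declared exploratory.

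**Level of detail.** An article may leave baseline definitions to a fuller document. That answers the measures for which a baseline could be defined. It does not answer the GQ: the article itself fixes the estimator, and no definition of baseline can give the GQ a pre-drug value.

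**Conclusion.** The point holds for the GQ and, as a smaller matter, for the IOS cohort item. For the GQ the stated d is undefined or, with session 1 as baseline, estimates D(1-f), which is between 0% and 100% of the final-session effect. Where in that range it falls cannot be said, because D and f are unknown. The step from undefined to attenuated rests on the assumption that session 1 would serve as baseline. That GQ has no pre-drug value rests on no assumption beyond the stated dosing and session schedule.

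For psychophysiology the document leaves a question to be answered, not a demonstrated error. The consequence is confined to exploratory estimates, but producing those estimates for future trials is one of the stated aims. The primary attendance comparison and its power statement are untouched.

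**What to change.** - **GQ:** replace the change score with a between-arm comparison of post-dose values, at the final session or averaged over sessions (choose one in advance). Allow for cohort membership, and standardise by the pooled within-arm SD of those same values.
- **IOS cohort item:** compare the single final value between arms in the same way.
- **Other outcomes:** keep change from baseline where a pre-dose value exists, and name that baseline for each outcome.
- **Psychophysiology:** state whether the 5-minute baseline recording precedes the spray, since this decides whether change from it retains an acute drug effect.

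For the GQ and the IOS item this is a change of analysis wording only, with no new data, visits or participants. The physiology point needs one clarifying sentence.

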#### Psychophysiology data collection

Participants and co-facilitators will each be equipped with a Zephyr™ BioHarness v3.0 (Zephyr Technology, Auckland, New Zealand), wearable, wireless, psychophysiology data collection equipment. Once a clear signal is established, participants will be comfortable seated for a silent, 5-min baseline physiology recording. The Zephyr™ TEAM System using OmniSense Software (Version 4.2.4) will record a continuous electrocardiogram (sampled at 250 Hz), respiratory rate, temperature, and three-axis accelerometry to measure posture and activity level throughout each 90-min MIGT session.

Psychophysiology data will be pre-processed using MindWare HRV software (v3.1.2, MindWare Technologies, Ltd., Gahanna, OH, USA). Artifacts will be identified via MindWare’s dual MAD/MED and IBI Min/Max artifact detection algorithms derived from established strategy [65] and then processed manually. High-frequency heart rate variability (HF-HRV) is used as an indicator of parasympathetic nervous system activity and a primary psychophysiological variable of interest with regard to human social behavior. HRV is reduced in methamphetamine users when compared to matched healthy controls [66], and oxytocin has been previously shown to increase HRV via variable changes of increased HF-HRV and decreased Detrended Fluctuation Analysis (DFA-1), which measures how “self-similar” the data are [67]. Evidence suggests that autonomic cardiac control may moderate the relationship between oxytocin and social behavior, and HRV may play a key role in psychiatric patient response in treatment trials of oxytocin [68].

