### Limitations and future directions

The current study will only include men who identify as having sex with men; therefore, results may not generalize to other genders and sexual orientations. There may be further selection bias regarding the motivation and engagement of participants who choose to take part in our study protocol. Furthermore, studies with substance use disorder populations often must deal with missing data from attrition. Our self-report measures increase the risk of reporting bias, although objective measures of psychophysiology will also be examined. Lastly, group therapy studies present inherent complications regarding statistical analyses. We will take these factors into account, although likely at the expense of statistical power. Despite these limitations, this study has many novel features and effect sizes will contribute to ongoing research. Future goals involve the further development of oxytocin-enhanced psychotherapy and expanding this treatment modality to other patient populations.

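### Secondary and exploratory effect sizes are fixed as unadjusted change-score differences, which are unbiased but less precise than baseline-adjusted differences where a pre-drug baseline exists

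*Protocol article*

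**What the plan says.** The Data Analysis Plan section of the protocol article sets the numerator: "Effect sizes will be calculated by subtracting the mean change in the oxytocin group from the mean change in the placebo group". The denominator comes from "dividing by the pooled baseline standard deviation". No baseline covariate enters the formula.

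The formula applies to the outcomes measured at every session ("Secondary outcomes collected at each MIGT session consist of group cohesion as measured by the GQ, self-reported anxiety as measured by the STAI-6", then psychophysiology, craving on the MCQ-Br and the urine drug screen). It also applies to the measures taken at baseline and after the last session, which "consist of the SRTB, SPS, IOS, and RTCQ and will be processed using the same methodology".

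The same section says the attendance analysis will "correct for interdependence resulting from MIGT cohort membership". For the secondary outcomes it promises only descriptive statistics and d. Mixed models or multiple imputation are to be considered if much data are missing. The Procedure section gives every member of a cohort the same study drug.

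The results are labelled exploratory. However, the end of the Background section makes effect-size estimation for future trials an aim, and Limitations and future directions says that "effect sizes will contribute to ongoing research".

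**The concern.** A raw change score subtracts the whole baseline value, although the outcome usually tracks baseline with a correlation below 1. The part subtracted in excess is noise. Regression on baseline subtracts only the predictable part, and it uses data that the trial already collects for the outcomes concerned.

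With 25 participants per arm, every d will be imprecise in any case. These estimates are a main secondary product of the trial and may be used to plan later ones, so avoidable noise in them has a cost. Two related matters affect how they will be read: whether an interval placed around d reflects the cohort structure, and whether a reader can tell which sign favours oxytocin.

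**Working it through.** **The plan's own figures.** The Power analysis section gives > 99% power at d = 1.44 and 80% at d = 0.81, with 25 per arm and two-sided alpha 0.05. A two-sample t-test with independent participants gives 0.9988 and 0.8013, so both reproduce. They concern attendance. No precision is stated for the secondary effect sizes.

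**Inputs.** From the protocol: n = 25 per arm; cohorts of four to six; one drug per cohort. Assumed: equal variances at both times, the baseline-outcome correlation rho, and the intracluster correlation (ICC).

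**Precision without clustering.** In baseline-SD units:
- variance factor of a change score: 2(1 − rho)
- variance factor of the baseline-adjusted difference: 1 − rho²
- ratio: 2(1 − rho) / [(1 − rho)(1 + rho)] = 2/(1 + rho)
- SE of d: √(2 × factor / 25), treating the SD in the denominator as known

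| rho (assumed) | Factor, change | Factor, adjusted | SE, change | SE, adjusted | Excess variance |
|---|---|---|---|---|---|
| 0.3 | 1.40 | 0.91 | 0.335 | 0.270 | 54% |
| 0.5 | 1.00 | 0.75 | 0.283 | 0.245 | 33% |
| 0.7 | 0.60 | 0.51 | 0.219 | 0.202 | 18% |
| 0.9 | 0.20 | 0.19 | 0.126 | 0.123 | 5% |

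At rho 0.5, a change-score d from 25 per arm is as precise as an adjusted d from 25 × 0.75 = 18.75, about 19 per arm.

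**Bias.** In simulations (five cohorts of five per arm, 4000 runs per setting, true effect 0.5), both estimators averaged between about 0.50 and 0.52 in every setting. The loss is in precision only. Without clustering, the ratios of simulated variances were (0.341/0.281)² = 1.47, (0.288/0.253)² = 1.30 and (0.230/0.214)² = 1.16 at rho 0.3, 0.5 and 0.7. These are slightly below the formula because the slope and the SD must be estimated. With ICC 0.10 on the residual and rho 0.5, the ratio was (0.340/0.310)² = 1.20, so clustering narrows the gain.

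**Cohort.** The design effect is 1 + (m − 1) × ICC. At m = 5 and an assumed ICC of 0.10 it is 1.4. An SE that ignores cohort would be 1/√1.4 = 0.845 of the correct one, about 15% too small. Over m = 4 to 6 and ICC 0.01 to 0.20, the correct SE is 1.015 to 1.41 times the naive one. The average d does not move.

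**Sign.** Suppose craving changes by −1.0 on oxytocin and −0.2 on placebo. The formula gives −0.2 − (−1.0) = +0.8. Suppose cohesion, scored so that higher is better, changes by +1.0 and +0.2. The formula gives 0.2 − 1.0 = −0.8. Both results favour oxytocin. Reversing the subtraction gives −0.8 and +0.8, which is still mixed. HF-HRV behaves like cohesion, since the psychophysiology section says "oxytocin has been previously shown to increase HRV via variable changes of increased HF-HRV".

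**The case against.** The case against is strong on several points, and most of it stands.

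- **Order of subtraction.** A reader might infer that taking placebo minus oxytocin causes the mixed signs. It does not: the scales have opposite good directions, and either order gives mixed signs. The order is fully stated, so each d can be read from its scale. This is a reporting matter and no estimate is wrong.
- **Clustering.** A reader might infer that leaving cohort out makes d biased or noisier. It does neither. It affects only an SE or interval, and the Data Analysis Plan does not commit to reporting one. Limitations and future directions also promises in general terms to deal with the statistical complications of group therapy, and the detail may properly lie in an analysis plan that is not shown.
- **Chance imbalance.** A reader might count imbalance at baseline as a second harm. A 0.3 SD imbalance does shift a change-score d away from the adjusted one by (1 − rho) × 0.3, which is 0.15 at rho 0.5. But 2(1 − rho) − (1 − rho²) = (1 − rho)², which is exactly the variance factor of that shift. It is the same loss seen another way. Nothing in the protocol supports a particular ICC at screening, before any group has met.
- **Scope.** Adjustment does not suit every outcome. The GQ rates relationships within the group, so no pre-drug baseline is evident. MCQ-Br timing is in a figure that is not shown. The text does not place the resting physiology recording before or after dosing. The urine screen is binary. Temperature has no stated beneficial direction.
- **Importance.** The outcomes are exploratory, and neither the primary analysis nor any test is affected.

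What this does not answer is that the article itself fixes the formula, and extends it to measures that do have a pre-drug baseline ("will be processed using the same methodology"). For those, a more precise estimate is available from the same data.

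**Conclusion.** The point holds in a limited form. For SPS, IOS, RTCQ, SRTB scores and STAI-6 (with the screening STAI state items as baseline), the prescribed d is unbiased on average but has a larger variance than a baseline-adjusted d. The excess is 54% at rho 0.3 and falls to 5% at rho 0.9. These figures assume equal variances at the two times, complete data and no clustering; rho is not given in the protocol. In the one clustered setting compared above (rho 0.5, ICC 0.10), the excess was about 20% rather than 33%.

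The documents do not support a claim that the effect sizes are biased, that the subtraction order is an error, or that a reported interval is wrong, since none is promised. The importance is modest. It rests on the stated aim of supplying effect sizes for future trials.

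**What to change.** Amend the effect-size sentence in the Data Analysis Plan:

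1. For continuous outcomes with a pre-drug baseline, take the numerator as the arm difference from a regression of the outcome on arm and baseline. Keep the pooled baseline SD as denominator.
2. Name the baseline reading for each outcome. Do not adjust for a first reading taken after the session-1 drug, and do not use this linear d for the urine screen.
3. If an interval accompanies d, have it account for cohort. Fifty participants in groups of four to six make about 8 to 12 cohorts (50/6 = 8.3; 50/4 = 12.5), so use a small-sample method and treat any ICC estimate as very imprecise.
4. State for each outcome which sign favours oxytocin. Where no direction is beneficial, as for temperature, state only which arm was higher.

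The cost is a few rewritten lines and a regression in place of a subtraction. The outcomes named in the verdict need no new data, and no hypothesis or sample size changes.

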## Background

Methamphetamine is a potent psychostimulant with high abuse potential [1]. Methamphetamine and amphetamine-type stimulants are second only to cannabis as the most frequently used illicit substance worldwide [2], and, according to the 2017 Global Drug Survey [3], methamphetamine was the illicit substance most likely to lead to emergency medical treatment seeking. High healthcare utilization contributes to the multifactorial economic burden of methamphetamine, which is estimated to be upwards of US$23.4 billion in the United States (US) alone (Rand Corporation, 2008). The prevalence of methamphetamine use disorder (MUD) in the US has risen dramatically in the past four decades, with high concentrations among men who have sex with men (MSM) [4–6]. Despite the personal and societal consequences of methamphetamine use, no pharmacological agent currently has an FDA-designated indication to treat MUD [7, 8].

Psychosocial treatment alone has been shown to reduce methamphetamine use and rates of relapse, with a longer duration of treatment producing better results [9–13]. However, methamphetamine users exhibit high attrition rates of 60% or more, which limits the effectiveness of treatment and leads to missing data and validity issues in clinical research contexts [14]. This complicates efforts to identify pharmacotherapy candidates or to improve evidence-based psychosocial treatments for MUD [8, 15]. Methamphetamine is associated with impairments in social cognition and theory of mind, including a hypersensitivity to social threat, which likely contribute to reduced treatment adherence and retention [16–19]. Social rehabilitation, often in the form of group and family therapy, is a prominent component of gold-standard psychosocial treatments for MUD [20, 21]. Even in animal models of methamphetamine addiction, socially housed—versus individually housed—rats were protected against escalating methamphetamine self-administration [22]. Given the social complexities and challenges surrounding MUD clinical treatment and research, an adjunctive pharmacotherapy that might enhance social cognition and boost engagement and retention in effective psychosocial treatment could greatly improve outcomes [23].

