Oxytocin administration in combination with evidence-based group psychotherapy—oxytocin-enhanced motivational interviewing group therapy (OE-MIGT)—may synergistically enhance treatment outcomes and address the notoriously high drop-out rates evident in MUD populations. We aim to investigate the effectiveness of intranasally administered oxytocin on MIGT treatment engagement. Specifically, we hypothesize that oxytocin will increase attendance at treatment sessions. In addition, we will estimate effect sizes and assess procedures used to test oxytocin’s effects on group cohesion, anxiety, psychophysiological stress reactivity, and stimulant craving and use for future trials. This novel translational protocol attempts to bridge ample animal data with the need for innovative clinical treatments for MUD.

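### Secondary effect sizes default to raw mean change, with missing-data models optional and no cohort term, although attendance itself is the hypothesised drug effect

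*Protocol article*

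**What the plan says.** All of this is in the protocol article.

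- **Estimator (Data Analysis Plan).** "Effect sizes will be calculated by subtracting the mean change in the oxytocin group from the mean change in the placebo group", and the result is divided by the pooled baseline standard deviation.
- **Where the data come from (Data Analysis Plan).** "Secondary outcomes collected at each MIGT session consist of group cohesion as measured by the GQ", followed by the STAI-6, psychophysiology, craving and the urine drug screen. A second set of questionnaires is handled the same way: "Additional exploratory outcome measures collected at two timepoints, baseline and after the final MIGT session".
- **Missing data (Data Analysis Plan).** "If there is substantial missing data, we also will consider using mixed linear models or multiple-imputation techniques". No threshold is given for when missingness counts as substantial, and no choice is made between the two methods.
- **Expected missingness (Background; Limitations and future directions).** "methamphetamine users exhibit high attrition rates of 60% or more, which limits the effectiveness of treatment and leads to missing data and validity issues". The limitations add that "studies with substance use disorder populations often must deal with missing data from attrition".
- **Hypothesis (Background).** "we hypothesize that oxytocin will increase attendance at treatment sessions".
- **Cohort.** Under Procedure, every member of a therapy cohort receives the same study drug. Cohorts have four to six members (MIGT section). The Data Analysis Plan corrects for cohort interdependence in the generalized estimating equations for attendance. It mentions no such correction for the secondary effect sizes.

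**The concern.** A man who is absent from a session presumably supplies no craving, anxiety, cohesion or physiology measurement for it. If oxytocin raises attendance as hypothesised, the oxytocin arm keeps men whom placebo would have lost. The observed mean changes then describe differently selected men, and randomisation no longer protects the comparison. The more the drug does for the primary outcome, the less comparable the arms become on the secondary ones.

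The article anticipates heavy attrition but treats it as a contingency. Whether to leave raw change, and for which alternative, is left open until the data are in, which adds avoidable discretion.

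Cohort is nested in arm, so ignoring it overstates how precisely d is known. This is the weaker limb, because it concerns precision and not bias. It still matters because the Background gives these effect sizes the purpose of informing future trials.

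**Working it through.** **1. The plan's own figures.** The Power analysis section gives more than 99% power at d = 1.44 and 80% at d = 0.81, with 25 per arm and two-sided alpha 0.05. A two-sample t-test gives 99.88% and 80.1%, so both reproduce. They concern the primary outcome and are not in dispute here.

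**2. Precision with fewer men.** If the change score has the same SD as baseline (baseline-final correlation 0.5), SE(d) ≈ √(2/n).
- n = 25 per arm: √(2/25) = 0.28.
- 60% attrition leaves 25 × 0.4 = 10 per arm: √(2/10) = 0.45.
- The ratio is √(25/10) = 1.58, a 58% increase. At correlation 0.6 the SD of change is √(2 × 0.4) = 0.89, so the SEs are 0.25 and 0.40, with the same ratio.

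**3. Bias from selective attendance (simulation, no true drug effect).** The documents give none of these inputs, so all are assumptions:
- standardised craving with baseline-final correlation 0.6;
- the chance of being seen at the end falls with current craving, by a log-odds of 0.5 to 1.5 per SD;
- end retention is 30–40% on placebo and 60–70% on oxytocin.

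The estimator is the plan's: difference in mean change among men seen, over their pooled baseline SD.
- Mildest setting (log-odds 0.5, 40% v 60%): mean changes −0.115 and −0.074; 0.041/0.99 = 0.04.
- Strongest setting (log-odds 1.5, 30% v 70%): mean changes −0.305 and −0.131; 0.174/0.95 = 0.18.

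The spurious d is therefore about 0.04 to 0.18. In this scenario it counts against oxytocin, because placebo retains only its lower-craving men. It would reverse if men who are doing well stay away. With equal retention in the two arms it is about zero.

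**4. Does modelling remove the bias?** It depends on why men are absent.
- *Absence depends on an earlier, observed score* (correlations 0.6; placebo retention 40%). The attender-only bias in the later score is 0.12 SD with 60% retained on oxytocin and 0.22 SD with 80%. Using the earlier score brings it to about 0.00.
- *Absence depends on current, unobserved craving* (step 3). Adjusting for baseline leaves a bias of roughly 0.06 to a little over 0.3, larger than for raw change.

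**5. Cohort.** Assume 10 cohorts of 5, so 8 degrees of freedom between cohorts within arms, and all 50 men observed. The design effect is 1 + (5 − 1) × ICC.
- Ignoring cohort: t(48) × 0.283 = 2.011 × 0.283 = 0.57.
- ICC 0.1: t(8) × 0.283 × √1.4 = 2.306 × 0.283 × 1.183 = 0.77.
- ICC 0.3: 2.306 × 0.283 × √2.2 = 2.306 × 0.283 × 1.483 = 0.97.

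**The case against.** The strongest reply is that this is a condensed article about exploratory outcomes. It already names mixed models and multiple imputation, acknowledges attrition, promises in general terms to take group-therapy complications into account, and says the secondary results need confirmation. No test, standard error or interval is claimed for them, so no precision claim is wrong. A spurious d of 0.04 to 0.18 is also small beside a standard error of 0.28 to 0.45.

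Much of this stands, and it limits the severity. It does not dispose of the point. The article does not merely leave the method to a later document: it fixes raw change as the default and makes the alternatives discretionary, against its own hypothesis and cited attrition. An exploratory label does not make a selectively observed d a sound planning value.

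Some stronger readings are not supported:

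- *That the plan prescribes a complete-case analysis of attenders.* It does not say so. This is an inference from where the data are collected, and the assessment timetable (Fig. 2) is not shown.
- *That the trial expects 60% attrition.* The figure is a background rate for methamphetamine users, not a planning assumption for this six-session study.
- *That a mixed model cures the problem.* Step 4 shows that it does so only when absence depends on observed data.
- *That absent men could simply complete the final questionnaires online.* Under Self-assessment measures, REDCap is used on study tablets, no remote link is described, and the SRTB is a structured interview.

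**Conclusion.** The concern holds as a matter of analysis choice and should be corrected; it does not threaten the trial's main result. The stated default is likely to compare differently selected men if the attendance hypothesis is true, and the choice of a better method is left until the data are seen. Cohort is ignored in the stated secondary estimator although it is nested in arm.

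The figures are illustrations. The bias of 0.04 to 0.18 rests on the assumed retention, correlation and attendance model, and its direction depends on who stays away. The 0.45 v 0.28 comparison applies the background attrition rate to both arms. The half-widths of 0.77 to 0.97 v 0.57 rest on assumed ICCs of 0.1 to 0.3 and 10 equal cohorts. The primary outcome, attendance, is recorded whether or not a man comes, so this missingness does not affect it.

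**What to change.** In the Data Analysis Plan, replace the conditional sentence with a commitment for the continuous session-level secondary outcomes:

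- a linear mixed model on all available sessions, with arm, session and the baseline value where one exists, and random intercepts for participant and cohort, whatever the amount of missing data;
- Cohen's d derived from that model with a 95% CI;
- a missing-not-at-random sensitivity analysis, for example shifting the unobserved values by a range of amounts that may differ by arm, because the main model removes bias only if absence depends on observed data.

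The raw mean changes can stay as description. The cost is a little more analysis work and wider stated intervals. With about 10 cohorts the ICC will be imprecise, and the report should say so. No new data collection is needed.
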